**4.2. Description of the study methodology****Study scheme (Figure 1)**

The tolerance study will be carried out by adapting the 2-step scheme of Simon (Simon, 1989) initially, and then by carrying out an increase in doses if tolerance is satisfactory.

From the data in the literature, it appears that the frequency of intolerance to treatment is <7% for a dose of 25 mg/day and <10% for a dose of 50 mg/day, which seems acceptable in this population and leads us to envisage a subsequent therapeutic trial. Conversely, its use does not appear possible if the respective frequencies are >15% and 20%, respectively.

In these conditions, for this tolerance study, we proposed a scheme which includes three successive stages combining the plan of Simon in two stages at a dose of 25 mg/day, and then an increase in dose to 50 mg/day with evaluation at a single time (Figure 1).

Under these conditions, the risk of not revealing unacceptable tolerance of eplerenone in this population is <10% and the risk of deciding, if tolerance permits, to not use it is 27%. There is a 60% chance of interrupting the study before the increase in dose if the hypothesis of unfavourable treatment is correct.

The advantages of the study scheme are that it will demonstrate unacceptable toxicity as early as possible and will detect a possible threshold effect between the doses of 25 mg/day and 50 mg/day which will allow the use of the lowest dose possible.

**Step 1:** 14 patients will be included in the first step, at an eplerenone dose of 25 mg/day. This stage will last 8 weeks. If  $\geq 3$  adverse events requiring the termination of treatment occur during these 8 weeks, the study will be stopped and the treatment will be considered to be too poorly tolerated to be used in this population. If <3 adverse events occur, we will proceed to step 2.

**Step 2:** This will consist of the addition of an additional 17 patients. All of the patients (14+17) will be treated with eplerenone at a dose of 25 mg/day for 8 weeks. If >4 adverse events requiring the termination of treatment occur during the 8 weeks, the study will be stopped and the treatment will be considered to be too poorly tolerated to be used in this population. If  $\leq 4$  adverse events occur, we will proceed to step 3.

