### 9.3. Size of the sample / population

#### 9.3.1 Calculation and/or justification of the number of subjects required

##### 9.3.1.1. Baseline hypothese(s) for this calculation:

According to data in the literature, the probabilities of hyperkalaemia developing during 8 weeks of eplerenone treatment are <7% with the 25 mg dose and <10% with the 50 mg dose (Gonzalez Monte *et al.*, 2010, Pitt *et al.*, 2003, Pitt *et al.*, 1999, Zannad *et al.*). We posed the alternative hypothesis that it is not useful to continue the study if the risk of hyperkalaemia is >15% with the 25 mg dose and 20% with the 50 mg dose.

The power for detecting an adverse event requiring the termination of treatment was fixed at 90%.

Under these hypotheses, it is possible to carry out a study in several steps by adapting the 2-step scheme proposed by Simon (Simon, 1989) in the following way:

First step: 14 patients will be included at the dose of 25 mg and followed for 8 weeks: if  $\geq 4$  patients experience an adverse event requiring the termination of treatment, the study will be stopped. In the opposite case, 17 additional patients will be included at the same dose for 8 weeks. If  $\geq 5$  patients out of the 31 have a limiting toxicity, the alternative hypothesis can be rejected and the study will be stopped; in the opposite case, the dose will be increased to 50 mg for 31 patients with a follow-up at 6 months. If at the end of this follow-up,  $\leq 4$  patients have a limiting toxicity with the 50 mg dose, the alternative hypothesis will be rejected and continuation of the study with eplerenone will be possible.

In these conditions, the probability of demonstrating a limiting toxicity greater than the fixed norms is 90.0%, the risk of stopping the study wrongly is 27.6%.

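### The step 1 stopping boundary is 3 of 14 in section 4.2 but 4 of 14 in section 9.3.1.1, and the stated 90.0% and 27.6% belong only to the first.

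*Protocol*

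**What the plan says.** Protocol section 4.2 describes step 1 as follows: "14 patients will be included in the first step, at an eplerenone dose of 25 mg/day". It then sets the rule in both directions: "If $\geq 3$ adverse events requiring the termination of treatment occur during these 8 weeks, the study will be stopped", and "If <3 adverse events occur, we will proceed to step 2".

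Section 9.3.1.1, the statistical justification, uses the same 14 patients but stops the study "if $\geq 4$ patients experience an adverse event requiring the termination of treatment". Otherwise, "17 additional patients will be included at the same dose for 8 weeks".

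The later boundaries agree. For step 2, section 4.2 stops "If >4 adverse events requiring the termination of treatment occur during the 8 weeks", and section 9.3.1.1 stops when five or more "patients out of the 31 have a limiting toxicity". For step 3, both sections accept the 50 mg dose at four or fewer failures.

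Directly after its own rules, section 9.3.1.1 states that "the probability of demonstrating a limiting toxicity greater than the fixed norms is 90.0%, the risk of stopping the study wrongly is 27.6"%. Section 9.3.1.3 repeats these as α = 27.6% and β = 10%. Section 4.2 gives a risk below 10% of missing unacceptable tolerance and a 27% risk of wrongly stopping.

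**The concern.** A stopping rule has to give one answer for every possible count. Here a count of three in step 1 gives two: stop for poor tolerance under section 4.2, or recruit 17 more patients under section 9.3.1.1. This is an open-label, single-arm safety study in patients for whom section 2.6 says the drug is currently contraindicated. If the boundary were chosen after three failures had been seen, the decision would depend on the data it was meant to judge.

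The statistical justification also needs its error rates to belong to its own rule. If 90.0% and 27.6% were computed for a boundary of three, then the design as written in section 9.3.1.1 does not have the power or the risk of wrongly stopping that it claims.

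**Working it through.** **Inputs, all from the protocol**

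- Step 1: 14 patients at 25 mg (sections 4.2 and 9.3.1.1).
- Step 2: 17 more at 25 mg, 31 in total; stop at 5 or more of 31 (both sections).
- Step 3: 31 patients at 50 mg; stop at 5 or more (the 31 is from section 9.3.1.1).
- Acceptable rates: 7% at 25 mg and 10% at 50 mg. Unacceptable rates: 15% and 20%.
- No loss to follow-up (section 9.3.1.5).
- Step 1 boundary s: 3 (section 4.2) or 4 (section 9.3.1.1).

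**Formula**

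Let X1 ~ Bin(14, p), X2 ~ Bin(17, p) and X3 ~ Bin(31, p′), independent, where p is the 25 mg rate and p′ the 50 mg rate.

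P(reach step 3) = Σ over x < s of P(X1 = x) × P(X2 ≤ 4 − x)

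P(stop at any step) = 1 − P(reach step 3) × P(X3 ≤ 4)

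**Terms of the sum**, P(X1 = x) × P(X2 ≤ 4 − x):

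| x | 15% rate | 7% rate |
|---|---|---|
| 0 | 0.1028 × 0.9013 = 0.0926 | 0.3620 × 0.9949 = 0.3602 |
| 1 | 0.2539 × 0.7556 = 0.1919 | 0.3815 × 0.9727 = 0.3711 |
| 2 | 0.2912 × 0.5198 = 0.1514 | 0.1867 × 0.8882 = 0.1658 |
| 3 (boundary 4 only) | 0.2056 × 0.2525 = 0.0519 | 0.0562 × 0.6638 = 0.0373 |

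For step 3, P(X3 ≤ 4) is 0.2287 at 20% and 0.8068 at 10%.

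**The protocol's figures, with boundary 3**

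- Unacceptable rates: 1 − 0.4359 × 0.2287 = 1 − 0.0997 = 0.9003, against the stated 90.0%.
- Acceptable rates: 1 − 0.8971 × 0.8068 = 1 − 0.7238 = 0.2762, against the stated 27.6%.

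Both agree to the first decimal.

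**The rule printed in section 9.3.1.1, with boundary 4**

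- Unacceptable rates: 1 − 0.4878 × 0.2287 = 1 − 0.1116 = 0.8884.
- Acceptable rates: 1 − 0.9344 × 0.8068 = 1 − 0.7538 = 0.2462.

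Other ways of counting were tried with boundary 4: step 3 only in patients still on treatment, cumulative counting across doses, conditional 50 mg rates, and step 2 counted afresh or in the 17 new patients only. None gives the pair 90.0% and 27.6%. The nearest, counting step 2 afresh in 31 patients, gives 90.4% and 25.4%.

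**Where the rules diverge**

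| | Boundary 3 | Boundary 4 |
|---|---|---|
| Stop in step 1, 15% rate | 35.2% | 14.7% |
| Stop in step 1, 7% rate | 7.0% | 1.4% |
| Stop before the dose increase, 15% rate | 56.4% | 51.2% |
| Stop at any step, 15%/20% | 90.0% | 88.8% |
| Stop at any step, 7%/10% | 27.6% | 24.6% |

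The first two rows differ by P(X1 = 3): 20.6% at a 15% rate and 5.6% at 7%.

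**The case against.** The strongest reply is that the protocol points to section 4.2 for conduct. Section 4.6.2 ends the study on the rule in section 4.2, section 4.6 cites Figure 1 and section 4.2, and section 9.1 cites section 4.2 for the primary criterion. Section 9.2 sends the reader to 9.3 only for the number of patients. The stated error rates also fit the section 4.2 rule. On this reading, section 9.3.1.1 contains one discrepant numeral. That is plausible, but no text gives either section precedence, and a wrong threshold in the statistical justification is still wrong.

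Second, the effect on the whole design is modest: 1.2 points of power, 3.0 points of wrong-stop risk and 5.2 points in the chance of stopping before the dose increase. The shared limit at step 2 acts as a backstop. After three failures in 14, boundary 4 allows at most one more in 17, which has a probability of about 25% at a 15% rate. This stands. The harm is mainly the contradictory instruction and the 17 further exposures in that branch.

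Third, section 4.2 counts adverse events and section 9.3.1.1 counts patients. One patient could meet two criteria at once, so the units are not strictly identical. But three patients, each with one terminating event, still get opposite instructions, so the wording does not reconcile 3 with 4.

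Fourth, sections 4.6 and 5.3.1 remove patients who have a terminating event, so step 3 may hold fewer than 31. With only the remaining patients, boundary 3 gives 86.3% and 24.7%, and boundary 4 gives 84.6% and 21.5%. Section 4.2 also quotes a 60% chance of interruption before the dose increase, which neither boundary reproduces. Both are separate matters and do not remove this contradiction.

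**Conclusion.** The concern holds and must be fixed. The two sections give different step 1 boundaries, and the difference decides what happens after exactly three failures. That outcome has a probability of about one in five if the true 25 mg rate is 15%.

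The stated 90.0% and 27.6% were computed for a boundary of three. The boundary of four, beside which they are printed, has 88.8% power and a 24.6% risk of wrongly stopping. Its miss risk of 11.2% exceeds both the chosen β of 10% in section 9.3.1.3 and the limit of under 10% in section 4.2.

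These results rest on the protocol's own rates, independent patients, no loss to follow-up and 31 patients in step 3. They identify the rule behind the stated figures. They do not say which boundary is clinically appropriate.

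**What to change.** Reconcile sections 4.2 and 9.3.1.1 to one step 1 boundary. Print all three boundaries in a single decision table, name the counting unit there, and have both sections refer to it. Beside the table, give the operating characteristics of the boundary kept, with the 31-patient assumption for step 3 stated:

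- boundary 3: 90.0% power and 27.6% risk of wrongly stopping;
- boundary 4: 88.8% and 24.6%.

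The cost is a wording amendment, with no extra patients and no new data. If four is kept, the amendment must also restate the error rates in sections 4.2, 9.3.1.1 and 9.3.1.3, and acknowledge that the 90% power target is narrowly missed.

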**Step 3:** This will consist of an increase in the dose of eplerenone to 50 mg/day in all patients who participated in step 2. The duration of this step will be 8 weeks. If  $\geq 5$  adverse events requiring the termination of treatment occur, the study will be stopped and the treatment will be considered to be too poorly tolerated to be used in this population. If  $\leq 4$  adverse events occur, the tolerance of eplerenone treatment in this population will be considered to be acceptable.

[figure not shown]

**Figure 1. Study scheme** showing the different possibilities

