##### **4.6.1 For participation of a patient in the study**

The participation of a patient finishes either at the end of the study (end of step 3) or after the development of an adverse event requiring the premature termination of eplerenone in this patient.

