### **9.3.1.2. Level of reference of the evaluation criterion and its variability**

The investigators anticipate a maximum of 15% adverse events requiring the stopping of eplerenone treatment in this population at a dose of 25 mg/day and 20% at a dose of 50mg/day. They do not foresee any variability for this evaluation criterion.

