### **9.3.1.3. Statistical risks chosen ( $\alpha$ , $\beta$ )**

The  $\alpha$  risk chosen is 27.6%.

The  $\beta$  risk chosen is 10%.

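### The stated 90.0% detection and 27.6% wrong stopping hold only if 20% (10%) is the risk of a new event after the rise to 50 mg and all 31 patients enter step 3; the protocol says neither

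*Protocol*

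**What the plan says.** **The limits.** Section 9.3.1.1 takes from the literature 8-week probabilities that "are <7% with the 25 mg dose and <10% with the 50 mg dose", and sets as unacceptable that the "risk of hyperkalaemia is >15% with the 25 mg dose and 20% with the 50 mg dose". Section 9.3.1.2 repeats the upper limits as rates "in this population at a dose of 25 mg/day and 20% at a dose of 50mg/day". Section 4.2 treats them in parallel: "Conversely, its use does not appear possible if the respective frequencies are >15% and 20%, respectively". None of these places describes 20% as the risk of a new event in a patient who has already tolerated 25 mg.

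**Who enters step 3.** Section 4.2 says of step 3: "This will consist of an increase in the dose of eplerenone to 50 mg/day in all patients who participated in step 2". Under section 4.6.1 a patient's participation ends "after the development of an adverse event requiring the premature termination of eplerenone in this patient". Section 4.6 makes withdrawal permanent, and section 5.3.3 provides for no replacement. By section 4.5.1, group A has spent 16 weeks and group B 8 weeks at 25 mg before the dose rises. Section 9.3.1.1 nevertheless counts 31 patients at 50 mg.

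**The operating characteristics.** Section 9.3.1.1: "In these conditions, the probability of demonstrating a limiting toxicity greater than the fixed norms is 90.0" per cent, with a 27.6% risk of stopping wrongly. Section 9.3.1.3: the β "risk chosen is 10" per cent. Section 4.2 gives the miss risk as below 10%, without conditions.

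**The concern.** The calculation treats step 3 as a new sample facing the whole 50 mg risk. In fact it is the remainder of the 25 mg sample after everyone with a stopping event has left. If the patients who fail at 25 mg are largely those who would also fail at 50 mg, part of the 20% has been used up before step 3 begins, and fewer new events are available to reach the limit of 5.

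This matters because stops at 25 mg supply only 56 of the 90 points of detection; step 3 must supply the other 34. This is a safety trial, and a pass opens the way to a later therapeutic trial. Its main statistical assurance is the miss risk below 10%, which is printed as a property of the design when it is a property of one undeclared assumption.

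**Working it through.** **Inputs.** Step 1: 14 patients, stop at 3 or more (section 4.2). Step 2: 17 more, stop at 5 or more of 31 (sections 4.2 and 9.3.1.1). Step 3: stop at 5 or more. Risks 15%/20% (unacceptable) and 7%/10% (acceptable). No loss to follow-up (section 9.3.1.5).

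**Model.** X ~ Bin(14, p) and Z ~ Bin(17, p) are the 25 mg failures. The trial reaches step 3 if X ≤ 2 and X + Z ≤ 4. Group A is given no further 25 mg events in step 2. Step 3 then stops if Bin(n, c) ≥ 5, where c is the new-event risk at 50 mg among patients who tolerated 25 mg.

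**The protocol's figures, n = 31:**
- p = 15%: P(stop before step 3) = 0.5641 (section 4.2 says 60%). P(Bin(31, 0.20) ≥ 5) = 0.7713. Detection = 0.5641 + 0.4359 × 0.7713 = 0.9003.
- p = 7%: P(stop before step 3) = 0.1029. P(Bin(31, 0.10) ≥ 5) = 0.1932. Wrong stopping = 0.1029 + 0.8971 × 0.1932 = 0.2762.

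Both match. With the step-1 limit of 4 or more printed in section 9.3.1.1, the results are 88.8% and 24.6%, which do not match.

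**Only patients still in the study, n = 31 − X − Z.** Given that step 3 is reached at p = 15%, n is 27, 28, 29, 30 or 31 with probability 0.350, 0.338, 0.216, 0.081 and 0.015. At c = 20% the chance of 5 or more events is 0.652, 0.685, 0.716, 0.745 and 0.771, which averages 0.686. Detection = 0.5641 + 0.4359 × 0.686 = 0.863. Wrong stopping at 7%/10% becomes 24.7%.

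**Overlap between doses.** If 15% and 20% are the risks of each dose in the whole population, and r is the proportion who would fail at both, then c = (0.20 − r)/0.85.
- No relation between doses: r = 0.15 × 0.20 = 0.03, so c = 0.17/0.85 = 20%.
- Complete overlap: r = 0.15, so c = 0.05/0.85 = 5.9%.

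The documents give no value for r, so it is varied here as an assumption:

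| New-event risk c in step 3 | Detection, 31 in step 3 | Detection, patients remaining |
|---|---|---|
| 20% | 90.0% | 86.3% |
| 15% | 78.5% | 74.5% |
| 10% | 64.8% | 62.7% |
| 5.9% | 57.9% | 57.4% |

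At 5.9%, step 3 adds about one point to the 56.4 from steps 1 and 2. Under the acceptable rates, complete overlap gives c = (0.10 − 0.07)/0.93 = 3.2% and wrong stopping of about 10.5%.

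**Group A in step 2.** The model gives the remaining group A patients no events in their second 8 weeks at 25 mg. With an assumed 5% risk there, detection (patients remaining) is 66.6% at c = 5.9% and 89.1% at c = 20%. With a fresh 15% it is 82.2% and 94.1%. Wrong stopping would also rise if group A carried such a risk under the acceptable rates.

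**The case against.** The strongest reply is that nothing has been miscalculated: 90.0% and 27.6% are exact for the rates assumed at each step. The design is sequential, the dose rises only if tolerance is satisfactory, and the step-3 rule counts limiting toxicities at 50 mg. Reading 20% as the limit among patients actually escalated fits that rule. Whether the literature rates for 50 mg came from patients raised from 25 mg cannot be seen from the protocol. This stands: the fault is an undeclared assumption, not an arithmetic slip, and a reader should not infer that 27.6% is simply wrong.

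A reader might also infer that true detection is 57%. The documents do not support that. It needs every patient who fails at 25 mg to be one who would fail at 50 mg, for a composite endpoint (section 4.1) that covers potassium, acidosis, two forms of hypotension, creatinine and any other unexpected event requiring termination. It also needs no further group A events in step 2. Section 2.4 expects the rise in potassium to peak at week 4, which makes some overlap plausible for hyperkalaemia, but says nothing about its degree.

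Finally, under complete overlap the escalated patients have a 5.9% new-event risk, below the protocol's acceptable 10%, so passing step 3 would be right for them. That also stands, and it is why the population to which the 50 mg conclusion applies has to be stated.

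The reply does not rescue the unconditional miss risk below 10%. The protocol's wording points to per-dose risks in the population, and even at a full 20% the patients remaining give 86.3% under the same model.

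**Conclusion.** The concern holds as an undeclared and favourable assumption behind the stated error rates. The figures 90.0%, 27.6% and below 10% are obtained with a step-1 limit of 3, a 20% (10%) risk of a new event after escalation, and 31 patients in step 3.

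On the patients who would actually enter step 3, the miss risk is 13.7% at a 20% step-3 risk. It rises with overlap to 25.5% at 15% and 37.3% at 10%, with 42.6% at 5.9% as the upper bound. These values assume no loss to follow-up and no further group A events in step 2; group A events in that period would raise detection. The extent of overlap is unknown, so the range is a sensitivity analysis and not an estimate.

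**What to change.** - In sections 4.2, 9.3.1.1 and 9.3.1.3, define the 10% and 20% step-3 limits as risks of a new limiting event after the rise to 50 mg in patients who tolerated 25 mg.
- Restate detection and wrong stopping on the patients who enter step 3: 86.3% and 24.7% with a step-1 limit of 3. State how group A's second 8 weeks at 25 mg are modelled.
- Replace the unconditional miss risk in section 4.2 with those figures and a short sensitivity range over the overlap between doses, labelled as an assumption, with 57.4% marked as a lower bound.
- Word the 50 mg conclusion as applying to patients already tolerant of 25 mg.
- Reconcile the step-1 limits of 3 (section 4.2) and 4 (section 9.3.1.1). Only 3 reproduces the stated figures; with 4, the patients remaining give 84.6% detection and 21.5% wrong stopping at the full 20% and 10%.

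The cost is a restatement in three sections. Apart from settling the conflicting step-1 limit, no patient number, visit or boundary changes. The downside is that the stated detection becomes less favourable.

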#### **4.6. Rules for permanent or temporary withdrawal from the study**

See Figure 1 and section 4.2

Withdrawal from the study is permanent: a patient who has left the study cannot re-enter the study.

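### The stated 90.0% detection and 27.6% wrong-stopping figures need 31 patients in the 50 mg step, but the withdrawal rules remove those who failed at 25 mg

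*Protocol*

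**What the plan says.** Section 9.3.1.1 sets acceptable event rates that "are <7% with the 25 mg dose and <10% with the 50 mg dose". The unacceptable level is a "risk of hyperkalaemia is >15% with the 25 mg dose and 20% with the 50 mg dose". The steps are:

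- **Step 1.** "14 patients will be included at the dose of 25 mg and followed for 8 weeks". Section 9.3.1.1 stops at 4 or more patients with a limiting event; section 4.2 stops at 3 or more.
- **Step 2.** A further 17 patients are added at 25 mg. The study stops at 5 or more of the 31.
- **Step 3.** If step 2 is passed, "the dose will be increased to 50 mg for 31 patients". Tolerance is acceptable if no more than 4 have a limiting toxicity at 50 mg.

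For this design, section 9.3.1.1 claims that "the probability of demonstrating a limiting toxicity greater than the fixed norms is 90.0%, the risk of stopping the study wrongly is 27.6" per cent. Section 9.3.1.3 repeats these as a beta of 10% and an alpha of 27.6%. Section 4.2 says that "the risk of not revealing unacceptable tolerance of eplerenone in this population is <10" per cent and adds: "There is a 60% chance of interrupting the study before the increase in dose if the hypothesis of unfavourable treatment is correct". The synopsis also gives 90% power.

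On leaving the study, section 4.6 says: "Withdrawal from the study is permanent: a patient who has left the study cannot re-enter the study". Section 4.6.1 ends participation at the event that stops eplerenone, section 5.3.1 lists those events as grounds for leaving, and section 5.3.3 marks replacement as not applicable.

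**The concern.** The power statement and the withdrawal rules use different denominators for step 3. A trial can pass step 2 with up to 4 patients already lost to limiting events at 25 mg. Those patients cannot be among the 31 whose dose is raised, yet the step-3 limit remains 4 events. Fewer patients against an unchanged limit make the 50 mg step easier to pass, so the more failures there are at 25 mg, the weaker the last safety check.

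The main statistical promise of this safety study is a high chance of recognising unacceptable tolerance. If the printed figures describe a design that the protocol's other sections do not allow, the surveillance committee and later readers are given a miss risk that is too low.

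**Working it through.** **Inputs.** Unacceptable rates are p = 0.15 at 25 mg and q = 0.20 at 50 mg; acceptable rates are p = 0.07 and q = 0.10 (section 9.3.1.1). Step sizes are 14 and 17. The step-1 stop s is 3 (section 4.2) or 4 (section 9.3.1.1). Step 2 is passed with at most 4 of 31, and step 3 with at most 4 events.

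**Formula.** Let a and b be the 25 mg failures among the first 14 and the next 17, and t = a + b. Then

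P(accept) = Σ over a < s and t ≤ 4 of Bin(a; 14, p) × Bin(b; 17, p) × P(Bin(n3, q) ≤ 4).

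Detection is 1 − P(accept) at 15%/20%. Wrong stopping is 1 − P(accept) at 7%/10%. Like the plan's figures, this gives each patient one 8-week risk at 25 mg and counts only 50 mg events in step 3.

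**1. Reproduce the plan (s = 3, n3 = 31).**
- At 15%/20%, P(reach step 3) = 0.4359 and P(Bin(31, 0.20) ≤ 4) = 0.2287. The product is 0.0997, so detection is 90.03%.
- At 7%/10%, 0.8971 × 0.8068 = 0.7238, so wrong stopping is 27.62%.

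Both printed figures are matched. With s = 4 and n3 = 31, detection is 1 − 0.4878 × 0.2287 = 88.8% and wrong stopping is 1 − 0.9344 × 0.8068 = 24.6%. The printed pair therefore rests on the section 4.2 boundary, not on the one printed beside it in 9.3.1.1.

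**2. Remove the 25 mg failures (n3 = 31 − t, s = 3, 15%/20%).**

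| t | n3 | P(t and reach step 3) | P(≤ 4 events at 20%) | Product |
|---|---|---|---|---|
| 0 | 31 | 0.0065 | 0.2287 | 0.0015 |
| 1 | 30 | 0.0355 | 0.2552 | 0.0091 |
| 2 | 29 | 0.0939 | 0.2839 | 0.0267 |
| 3 | 28 | 0.1473 | 0.3149 | 0.0464 |
| 4 | 27 | 0.1527 | 0.3480 | 0.0531 |

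The products sum to 0.137, so the miss risk is 13.7% and detection 86.3%. A full 31 is rare here: 0.0065/0.4359 = 1.5% of trials that reach step 3. In (0.1473 + 0.1527)/0.4359 = 69% of them, 27 or 28 patients remain.

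**3. All results.**

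| Step-1 stop | Step-3 number | Detection | Miss | Wrong stopping | Stopped before dose increase, at 15% |
|---|---|---|---|---|---|
| ≥ 3 | 31 fixed | 90.0% | 10.0% | 27.6% | 56.4% |
| ≥ 3 | failures removed | 86.3% | 13.7% | 24.7% | 56.4% |
| ≥ 4 | 31 fixed | 88.8% | 11.2% | 24.6% | 51.2% |
| ≥ 4 | failures removed | 84.6% | 15.4% | 21.5% | 51.2% |

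The last column does not depend on n3: 1 − 0.4359 = 56.4% and 1 − 0.4878 = 51.2%, against the stated 60%.

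**4. Group A's second 8 weeks.** Section 4.2 treats group A at 25 mg again during step 2. The documents give no risk for that period, so I assumed 2% to 15% (s = 3, failures removed).
- If steps 1 and 2 are counted together, detection is 87.4% at 2%, 89.1% at 5%, 90.5% at 7.5%, 91.8% at 10% and 94.1% at 15%.
- If only events in the step-2 weeks are counted, it runs from 81.1% at 2% to 87.6% at 15%.

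**The case against.** The strongest reply is that 86.3% belongs to one model. Group A spends 16 weeks at 25 mg. If its later events count toward the 31-patient limit, an assumed second-period risk of about 7.5% or more brings detection back above 90% even with failures removed. That stands: a reader might infer that the design certainly misses its 90% target, and the documents do not go so far. They do not say how those weeks count, and section 4.2 (events during the 8 weeks) and section 9.3.1.1 (patients out of 31) can be read differently. It does not rescue the printed figures, which leave those weeks out and match the fixed-31 calculation.

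One could also count 25 mg failures toward the step-3 limit. With a 20% risk among those remaining, detection would be 98.7%, but wrong stopping would be 59.0%. That fits neither the printed 27.6% nor the wording of 9.3.1.1, which counts toxicity at 50 mg.

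The stated 60% could be coarse rounding, since section 4.2 also gives 27% for 27.6%. Cumulative counting with a 2% second-period risk also gives about 60%. This part is minor, but neither boundary yields 60% under the model behind the 90.0%.

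Two further inferences are not supported:

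- **Adding failures across doses.** Four failures at 25 mg plus four at 50 mg make 8/31 = 26%, which looks worse than the 20% limit. The limits are set per dose, and four events among 27 entrants is 14.8%.
- **A fixed range of 27 to 31 in step 3.** This needs cumulative counting and no other exits. If only step-2 events count, 2 in step 1 and 4 in step 2 leave 25. Section 5.3.1 also removes patients who need a contraindicated drug.

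**Conclusion.** The point holds. The printed 90.0% and 27.6% describe a design in which 31 patients always enter the 50 mg step, and the protocol's withdrawal and replacement sections rule that out once anyone has failed at 25 mg. Changing only the step-3 number lowers detection by 3.7 points to 86.3%, raises the miss risk from 10.0% to 13.7%, and lowers wrong stopping to 24.7%. With the step-1 boundary printed in 9.3.1.1 the values are 84.6%, 15.4% and 21.5%. The lower wrong-stopping risk is a gain, but it does not meet the detection target that the plan fixed.

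The result assumes independent patients, the plan's event rates, one 8-week risk at 25 mg, only 50 mg events counted in step 3, and no exits for other reasons. Group A's second period could move detection to between about 81% and 94% under the 3-or-more rule. A single replacement figure therefore has to wait until the boundary and the counting are settled.

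**What to change.** 1. Reconcile the step-1 boundaries in sections 4.2 and 9.3.1.1 (3 or more against 4 or more of 14). The printed figures match the former, but which rule applies is for the sponsor to decide.
2. In section 9.3.1.1, replace the reference to 31 patients at 50 mg with the patients remaining on treatment after step 2, as sections 4.6 to 5.3.3 already require.
3. State whether group A's events in its second 8 weeks at 25 mg count toward the 31-patient limit.
4. Restate detection, wrong stopping and early stopping on that basis in sections 4.2, 9.3.1.1 and 9.3.1.3, and the power in the synopsis. Under the 3-or-more rule with no further group A events these are 86.3%, 24.7% and 56%; under the 4-or-more rule, 84.6%, 21.5% and 51%. If a second-period risk is assumed, state it and recompute.

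The cost is a recalculation and text changes, with no extra patients. The downside is a stated power that may be less favourable than the 90% target. If the sponsor wants to keep 90%, the design has to be re-derived, and whether that needs more patients has not been worked out here.
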